### **13.3 Appendix 3. Taliglucerase alfa Hypersensitivity Evaluation and Treatment Algorithm**

During and after infusion of taliglucerase alfa, the following algorithm will be followed to monitor and manage the occurrence of hypersensitivity, anaphylaxis, or anaphylactoid reactions.

#### **Clinical signs**

##### Early

- Sensation of warmth and itching
- Feelings of anxiety or panic

##### Moderate

- Pruritus
- Flushing
- Urticaria
- Chest discomfort
- Mild Hypotension

##### Progressive

- Erythematous or massive urticarial rash
- Edema of face, neck, soft tissues

##### Severe

- Hypotension
- Bronchospasm (wheezing)
- Laryngeal edema (dyspnea, stridor, aphonia, drooling)
- Arrhythmias

#### **Treatment algorithm**

With the onset of any of the above clinical signs, immediately discontinue study medication administration and initiate the following monitoring.

- Continuous electrocardiographic monitoring
- Continuous pulse oximetry
- Measure blood pressure every 5 minutes
- Perform chest auscultation every 5 minutes

- 
- Blood samples need to be collected for Tryptase (29-33) and antibodies. Tryptase samples need to be withdrawn at:
    - 1st sample taken 0.25-3 hours after onset of symptoms
    - 2nd sample taken between 3-6 hours
    - 3rd sample taken 24-48 hours to verify the return to baseline.

In the case of progressive or severe hypersensitivity, treat appropriately and withdraw the subject from the study.

Treat as follows:

Urticaria or edema of the face, neck, or soft tissues

- Epinephrine 1:1000 solution, 0.5 mL subcutaneously, repeat as needed every 5-10 minutes
- Antihistamines
- Corticosteroids

Hypotension (systolic blood pressure (SBP)  $\leq$  90 mmHg)

- Isotonic sodium chloride solution, 1 L every 30 minutes as needed to maintain SBP > 90 mmHg
- Epinephrine 1:10,000 solution given IV at 1 µg/minute initially, then 2-10 µg/minute to maintain SBP > 90 mmHg
- Norepinephrine 4 mg in 1 L 5% dextrose in water given IV at 2-12 µg/min to maintain SBP > 90 mmHg
- Glucagon 1 mg in 1 L 5% dextrose in water give IV at 5-15 µg/minute for refractory hypotension

Bronchospasm

- Oxygen by face mask at 6-8 L/minute to maintain oxygen saturation at > 90%
- Epinephrine 1:1000 solution, 0.5 mL subcutaneously
- Albuterol 0.5 mL of 0.5% solution in 2.5 mL of sterile saline every 15 minutes up to three doses
- Inhaled beta-agonists
- Corticosteroids

Laryngeal edema

- Epinephrine 1:1000 solution, 0.5 mL subcutaneously, repeat as needed every 5 to 10 minutes
- Corticosteroids

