#### **6.3.3 Removal of Subjects from Therapy or Assessment**

Reasons for permanent discontinuation include the following:

- The subject experiences two or more Grade 3 toxicities or one or more Grade 4 toxicity considered by the investigator associated with taliglucerase alfa treatment (see Sections 8.2.4 Adverse Events and 13.5, Appendix 5 WHO Common Toxicity Criteria)

- Subjects who experience progressive hypersensitivity or severe hypersensitivity will be treated appropriately and withdrawn from the study (see Appendix 2 and Appendix 3)
- The subject requests to discontinue treatment
- Investigator feels that it is not in the best interest of the subject to continue treatment and/or if the investigator believes the subject can no longer be compliant with the requirements of the study.

For any discontinuation, the Investigator will obtain all the required details and document the date and the main reason for the premature termination. If the reason for discontinuation is an adverse event, the specific event or the main laboratory abnormality will be recorded in the CRF. The Investigator will make thorough efforts to document the outcome. The Investigator will attempt to continue to follow the subject for the full duration of the study or at least for 30 days following discontinuation. If circumstances prevent the subject from completing all visits, every attempt will be made to complete all procedures listed in Section 9 for Visit 28.

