9. DEXA
10. Taliglucerase alfa infusion

Perform the following procedures for taliglucerase alfa dosing:

- Observe the subject clinically for a minimum of 1 hour after dosing
- Evaluate vital signs every 30 minutes
- Evaluate the injection site.

Protocol Number PB-06-005

Protalix Ltd.  
April 28, 2010

---

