**13.2 Appendix 2. Infusion Rate Algorithm**

The infusion rate (IR) may be adjusted according to individual subject symptoms and signs. The assumptions with respect to adverse experiences to the infusion are:

1. Most of the subjects will tolerate the infusion without any special symptom or event. The infusion rate may be increased over time to the maximal rate 2.25 ml/minor after discussion with the Medical Monitor (an infusion duration of 1 hour).
2. Subjects presenting symptoms and signs of **severe** hypersensitivity will be evaluated according to the WHO Drug Toxicity criteria and there may be a discontinuation of treatment according to the protocol.
3. Subjects may present signs and symptoms that will respond to reducing of the infusion rate and may not appear at the next infusion.
4. Tolerability and the subject specific infusion rate will be assessed and decided by the Investigator according to vital signs and clinical status of the subject.

Definitions to be applied regarding tolerability of infusions are as follows:

| Good tolerability                                                                                                       | Partial tolerability                                                                                                           | Poor tolerability                                                                                                                                                            |
|--------------------------------------------------------------------------------------------------------------------------------|---------------------------------------------------------------------------------------------------------------------------------------|-------------------------------------------------------------------------------------------------------------------------------------------------------------------------------------|
| Infusion was performed without Signs and symptoms (such as burning, pruritus, flushing, discomfort, or change in vital signs). | Signs and symptoms appeared during the infusion and resolved after slowing infusion rate or at the end of the infusion. | Signs and symptoms meeting the definitions of WHO Grade 1 or 2 toxicity responding to reduction of infusion rate or responding to treatment (example, antihistamine for urticaria). |

The specific algorithm to be followed is below.

[figure not shown]

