| Category                | Toxicity                | Grade0                                     | Grade1                                      | Grade2                                                  | Grade3                                                       | Grade4                                                               |
|-------------------------|-------------------------|--------------------------------------------|---------------------------------------------|---------------------------------------------------------|--------------------------------------------------------------|----------------------------------------------------------------------|
| Allergy                 | Allergy                 | none                                       | transient rash, drug fever < 38°C (100.4°F) | urticaria, drug fever 38°C (100.4°F), mild bronchospasm | serum sickness, bronchospasm requiring parenteral medication | anaphylaxis                                                          |
| Local                   | Local                   | none                                       | pain                                        | pain and swelling with inflammation or phlebitis        | ulceration                                                   | plastic surgery indicated                                            |
| Fever of unknown origin | Fever of unknown origin | none                                       | 37.1 - 38.0° C 98.7° - 100.4° F             | 38.1 - 40.0°C 100.5 - 104°F                             | > 40.0°C > 104.0°F for less than 24hrs                       | > 40.0°C (>104°F) for more than 24 hrs or accompanied by hypotension |
| Infection               | Infection               | none                                       | mild                                        | moderate                                                | severe                                                       | life-threatening                                                     |
| Additional events       | Asthenia                | Analogous to Karnofsky index (WHO grading) |                                             |                                                         |                                                              |                                                                      |

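### The printed instructions for infusion reactions conflict between Appendix 2, Appendix 3, Appendix 5 and Section 6.3.3, and the early-stop visit literally includes a study-drug infusion

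*Protocol*

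**What the plan says.** Four parts of the protocol govern a reaction to the infusion.

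- **Appendix 2 (infusion rate).** Among its assumptions: "Subjects may present signs and symptoms that will respond to reducing of the infusion rate and may not appear at the next infusion". Its table defines good, partial and poor tolerability. The signs named include pruritus and flushing. Partial tolerability covers signs that go away once the rate is slowed or when the infusion ends. Poor tolerability covers WHO Grade 1 or 2 signs that respond to a lower rate or to treatment, with an antihistamine for urticaria as the example. The algorithm itself is a figure that is not available here.
- **Appendix 3 (hypersensitivity).** Signs are sorted into Early (including itching), Moderate (including pruritus, flushing, urticaria and *Mild Hypotension*), Progressive, and Severe (including *Hypotension* and "Bronchospasm (wheezing"). The instruction for all tiers is: "With the onset of any of the above clinical signs, immediately discontinue study medication administration and initiate the following monitoring". Progressive or severe reactions lead to withdrawal.
- **Appendix 5 (toxicity grades).** Allergy Grade 2 reads: "urticaria, drug fever 38°C (100.4°F), mild bronchospasm".
- **Section 6.3.3 (removal of subjects).** Subjects with progressive or severe hypersensitivity "will be treated appropriately and withdrawn from the study (see Appendix 2 and Appendix 3". For those who cannot complete all visits, "every attempt will be made to complete all procedures listed in Section 9 for Visit 28". The Visit 28 list in Section 9.2.10 contains "10. Taliglucerase alfa infusion", and the flow chart also marks an infusion at that visit.

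**The concern.** These are operative safety instructions for children aged 2 to under 18 years. Staff who consult one appendix would slow a running infusion. Staff who consult another would stop it, and for some signs would also withdraw the child. Neither would be departing from the protocol.

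For the analysis, the amount infused, the infusion rate reached, the number of permanent discontinuations and the tier given to a reaction could partly depend on which page a site followed. The trial plans 10 subjects at 5 to 10 sites, an average of 10/10 = 1 to 10/5 = 2 subjects per site, and withdrawn subjects are not replaced. Differences between sites therefore cannot be expected to average out when discontinuations or hypersensitivity events are set side by side for the two doses.

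**Working it through.** The plan gives no figure to reproduce and no arithmetic applies. The check follows one reaction at a time through the printed text.

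| Reaction | Appendix 2 | Appendix 5 | Appendix 3 | Section 6.3.3 |
|---|---|---|---|---|
| Pruritus, flushing | Named; partial tolerability if it settles after slowing or at the end of the infusion | – | Moderate (itching is Early): stop administration at onset | – |
| Urticaria | Example under poor tolerability, responding to treatment | Allergy Grade 2 | Moderate: stop at onset | – |
| Mild bronchospasm | Poor tolerability, if it responds to a lower rate or treatment | Allergy Grade 2 | Severe (no mild category): stop and withdraw | Withdraw |
| Hypotension | Poor tolerability, if Grade 1 or 2 and it responds | Grade 2 if it needs fluids or other therapy without hospital admission | Moderate if mild, otherwise Severe: stop; withdraw if Severe | Withdraw if Severe |

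**(a) Slow or stop.** Appendix 2's partial class presupposes that the infusion went on after the sign appeared: the sign either settled at a slower rate or lasted until the end. Appendix 3 requires administration to stop at onset. For pruritus and flushing, which both texts name, a site that obeys Appendix 3 to the letter would not see the course that Appendix 2 describes, unless the infusion is restarted and the sign recurs.

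**(b) Grade and tier.**
- Mild bronchospasm is Grade 2 on one scale and Severe on the other. The first can place the infusion in a tolerability class. The second ends the child's treatment.
- For hypotension, the Appendix 3 tier lists separate Moderate from Severe only by the word *mild*. The one figure given, a systolic pressure of 90 mmHg or less, stands in the treatment heading and is not tied to either tier. A site therefore cannot tell from the text which hypotension triggers withdrawal.

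**(c) Early-stop visit.** Step 1: progressive or severe hypersensitivity is listed in 6.3.3 among the reasons for permanently ending treatment. Step 2: for any discontinuation in which the remaining visits cannot be completed, 6.3.3 asks for all Visit 28 procedures. Step 3: item 10 of Visit 28 is a study-drug infusion. Read literally, a child withdrawn for a severe reaction is scheduled for another infusion. No exception is printed in 6.3.3 or 9.2.10.

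**The case against.** The strongest reply is that the Appendix 2 table only classifies infusions and that its actions are in a figure not seen here, which may give a stop-then-restart sequence. Appendix 3's order most naturally means interrupting the current infusion, not ending treatment. Its premedication text foresees later infusions after early signs and refers to Appendix 2 for rate adjustment. Two scales can also coexist, because 6.3.3 lists WHO-grade toxicity and hypersensitivity as separate triggers. This narrows the point but does not remove it. Stopping an infusion and slowing it are still different instructions, and the wording of the Appendix 2 definitions still implies an infusion that continued.

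A reader might infer more than the documents support:

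- **Withdrawal itself is contradictory.** Appendix 2 says of severe reactions that "there may be a discontinuation of treatment according to the protocol", whereas 6.3.3 and Appendix 3 make withdrawal certain. The clause defers to the protocol, and the other two passages agree. At most the wording should be aligned.
- **Outcome data are lost from children who react.** Section 6.3.3 asks the investigator, after any discontinuation, to try to follow the subject for the full study or at least 30 days.
- **The fixed treatment amounts and the single blood pressure figure are wrong for this age range.** No other passage contradicts them. That is a clinical judgement, it would need body weights the protocol does not give, and no view is taken here.
- **The pivotal study's 2 hypersensitivity discontinuations among 32 patients measure the problem.** They count discontinuations, not reactions on which these passages disagree, and come from a 38-week study. Expressing a loss as a share of one arm would also assume an allocation ratio that Section 7.7 does not state.

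**Conclusion.** The concern holds for three printed conflicts: slowing against stopping for signs named in both appendices; the grade and tier of mild bronchospasm, with an undefined boundary for hypotension; and an early-stop visit that includes an infusion after treatment has been permanently discontinued.

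The third is literal, though probably a drafting oversight. The bronchospasm mismatch is also plain in the text; that it produces two different actions rests on the reaction responding to a lower rate or treatment, as Appendix 2's definition requires. How far the first affects practice depends on the unseen flow figure. The documents give no basis for estimating how often a site would meet any of these conflicts, so the size is stated as the number of conflicts and not as a probability. The point warrants an amendment because following the safety text as written can lead to different actions for the same reaction in a child.

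**What to change.** The sponsor's clinical team must reconcile Appendix 2 (including its flow figure), Appendix 3, Appendix 5 and Section 6.3.3, so that each sign carries one grade and one action and the two hypotension entries have a stated boundary. It must also reconcile the early-stop instruction in 6.3.3 with item 10 of Visit 28, so that the text says explicitly how the infusion is treated for subjects whose treatment has ended. The Appendix 2 clause on severe reactions can be aligned with 6.3.3 in the same pass. Which clinical rule is right is for that team; none is proposed here.

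The cost is a protocol text amendment, with no new visits, assessments or data.

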### **7.4 Study Drug Administration**

For initial infusions in all subjects, taliglucerase alfa will be administered at a rate of 1.2 mL/min over 2 hours. The tolerability of the infusion will be determined by signs and symptoms during the infusion for one hour after the infusion in the clinic and by telephone contact the day after the infusion. If this rate of infusion is well tolerated, the rate of infusion may be increased up to 2.25 mL/min to deliver the 135 mL volume over one hour for all subsequent dosing after discussion with the Medical Director. The infusion rate may be adjusted according to individual subject symptoms and signs (see Section 13.2, Appendix 2).

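### The visible texts of Appendices 2 and 3 are not aligned on handling pruritus, flushing or urticaria during an infusion, and Poor tolerability can take in a sign that requires withdrawal

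*Protocol*

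**What the plan says.** Section 7.4 states that "The infusion rate may be adjusted according to individual subject symptoms and signs" and refers to Appendix 2. Appendix 2 lists as one of its assumptions: "Subjects may present signs and symptoms that will respond to reducing of the infusion rate and may not appear at the next infusion". It then defines three tolerability classes.

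- **Good:** "Infusion was performed without Signs and symptoms (such as burning, pruritus, flushing, discomfort, or change in vital signs").
- **Partial:** signs arose during the infusion "and resolved after slowing infusion rate", or by the time the infusion ended.
- **Poor:** WHO Grade 1 or 2 signs that responded to a lower rate or to treatment. The example given is an antihistamine for urticaria.

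The algorithm itself is a figure that is not reproduced in the text available.

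Appendix 3 opens with: "During and after infusion of taliglucerase alfa, the following algorithm will be followed". Its Early tier includes "Sensation of warmth and itching". Its Moderate tier includes pruritus, flushing and urticaria. Its Severe tier includes bronchospasm. The action is common to all tiers: "With the onset of any of the above clinical signs, immediately discontinue study medication administration and initiate the following monitoring". The tiers then decide withdrawal: "In the case of progressive or severe hypersensitivity, treat appropriately and withdraw the subject from the study". Section 6.3.3 repeats that withdrawal rule.

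**The concern.** The same sign in the same child appears under two texts that point to different actions. Someone working from Section 7.4 and Appendix 2 could slow the infusion for flushing or itching and watch for it to settle. Someone working from Appendix 3 would stop, start continuous ECG and oximetry, check blood pressure and chest every 5 minutes, and draw three tryptase samples.

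These are foreseeable reactions. Section 4 reports hypersensitivity and pruritus among the related events seen at increased frequency in the pivotal study, and two of its patients discontinued for a hypersensitivity reaction. About 10 children are spread over 5 to 10 sites (Section 13.4.1), and after Month 3 infusions may move to the home or an infusion centre under local procedures (Section 9.2.4). Few sites will see enough cases to settle on a shared practice, so the written rule matters.

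Two things are at stake: consistent and safe handling of infusion reactions, and a tolerability class that means the same thing at every site.

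**Working it through.** No power, error rate or sample size figure is involved, so the check sets the texts side by side.

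| Sign | Appendix 2, visible text | Appendix 3 tier | Appendix 3 action |
|---|---|---|---|
| Itching / pruritus | Pruritus is an example of a sign absent under Good; if present, classed by how it resolves | Early (itching), Moderate (pruritus) | Stop at onset |
| Flushing | As for pruritus | Moderate | Stop at onset |
| Urticaria | Example under Poor, treated with an antihistamine | Moderate | Stop at onset |
| Mild bronchospasm | Falls within Poor through WHO Grade 2 allergy (Appendix 5) | Severe (bronchospasm, no mild exception) | Stop at onset and withdraw |

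**Step 1: does Appendix 3 set a threshold for stopping?** No. The trigger is the onset of any listed sign. The tiers matter only for withdrawal, which is limited to progressive or severe hypersensitivity.

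**Step 2: can the Appendix 2 classes be reached if Appendix 3 is followed?** Resolution after slowing presupposes that the infusion is still running. Once the infusion is stopped at onset, that limb cannot be observed for pruritus or flushing. On the natural reading, nor can persistence to the end of the infusion. Poor can still be reached through response to treatment, but not through response to a lower rate.

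**Step 3: does any visible sentence reconcile the two?** The premedication text in Appendix 3 refers to Appendix 2 for rate adjustment, but it concerns subsequent infusions and not the one in progress. Appendix 2 leaves tolerability and rate to the investigator, but does not say that this judgement overrides the stop.

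**Step 4: Poor tolerability against withdrawal.** Poor admits WHO Grade 1 or 2 signs. Appendix 5 places mild bronchospasm in Grade 2 allergy. Appendix 3 lists bronchospasm as Severe, and Section 6.3.3 withdraws subjects with severe hypersensitivity. A child with mild bronchospasm that settles could therefore be classed as Poor, as a matter of rate and treatment, while Appendix 3 and Section 6.3.3 require withdrawal.

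**Step 5: exposure per site.** 10 children / 10 sites = 1, and 10 children / 5 sites = 2, so an average of one to two children per site.

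No count of overlapping signs is offered. Discomfort and change in vital signs in Appendix 2 may or may not correspond to chest discomfort and mild hypotension in Appendix 3, so any total would rest on judgement.

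**The case against.** The strongest reply is that the operative half of Appendix 2 is its figure, which cannot be seen here. The visible text offers only assumptions and definitions, and no sentence in it orders staff to slow for pruritus or flushing. Those two signs are named only as examples of what is absent under Good. If the figure has a stop-then-resume step, or sends listed signs to Appendix 3, much of the mismatch goes. This stands, and it limits the finding to the printed wording. A reader might infer that the protocol has no restart or precedence rule at all, or that it gives two flatly opposed orders. The documents do not support either inference.

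A second reply is that the appendices serve different purposes: one sets the infusion rate and the other manages hypersensitivity. That is true of their titles, but Appendix 3 is triggered by the sign and not by a diagnosis. No visible criterion separates rate-related itching from early hypersensitivity itching.

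A third is that discontinuing administration may mean halting only the current infusion. That is the better reading, because permanent withdrawal is dealt with separately and children with early signs are expected to receive further infusions. A reader might infer that itching or flushing ends a child's participation, and the text does not say so. Even a halt differs from slowing, and it sets off the monitoring and sampling.

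Finally, the unconditional stop is worded more strongly than the permissive rate adjustment, so a cautious site would follow Appendix 3. That softens the problem, but leaves precedence to be inferred at the bedside. Appendix 2 does mention severe hypersensitivity separately, but only as something assessed by WHO criteria that may lead to discontinuation. That does not clearly catch a Grade 2 bronchospasm.

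**Conclusion.** The point holds in limited form and is minor. In the visible text, Section 7.4 and Appendix 2 contemplate slowing, and class signs by their response to slowing or treatment, while Appendix 3 requires an immediate stop at the onset of signs that Appendix 2 also names: pruritus/itching, flushing and urticaria. Independently, Poor tolerability takes in mild bronchospasm through WHO Grade 2 allergy, although Appendix 3 and Section 6.3.3 require withdrawal for bronchospasm.

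The conclusion rests on two readings: that itching and pruritus are the same sign for this purpose, and that the Severe tier includes bronchospasm of any degree because no mild exception is stated. It makes no claim about what the unseen figure contains.

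Different handling between sites is possible but not shown. A reader might infer an effect on dose delivered or on the efficacy results. The protocol gives no frequency for these signs within the planned trial, so no such effect can be estimated. Sample size, power and the primary analysis are unaffected.

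**What to change.** Amend Appendix 2 in three places.

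1. **Precedence and restart.** State that for any sign listed in Appendix 3 the infusion is first stopped as that appendix requires. After an Early or Moderate sign has resolved, the investigator may resume at a reduced rate. Check this sentence against the Appendix 2 figure so that the two agree.
2. **Class definitions.** In Partial, let the sign resolve *after slowing or interrupting the infusion, or at the end of the infusion*. In Poor, let it respond *to reduction or interruption of the infusion, or to treatment*. Keep the WHO grade condition and the treatment limb in Poor, so that the two classes stay distinct.
3. **Exclusion.** State that Poor does not include any sign that Appendix 3 lists as Progressive or Severe. Those lead to withdrawal under Section 6.3.3.

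The cost is a short amendment and a notice to sites, with no extra patients or visits. The downside is that some infusions will be interrupted that might have settled on slowing alone. Keeping the stop as the governing rule is the cautious choice. The sponsor could instead limit Appendix 3 to suspected hypersensitivity, but it would then have to supply the criterion for suspecting it, which the visible text lacks.
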